**Figure 5 fig5:**
[figure not shown]
Strolll AR web portal for therapists to (remotely) prescribe individualized treatment programs (type and settings of AR exercises, top part) and to see feedback on adherence and game-play performance (session history, lower part).

#### Final assessment (T2): effectiveness and clinical feasibility

2.2.7

To be able to evaluate the effectiveness of the Strolll AR intervention, the therapist will again administer standard clinical tests of gait, balance, and falls risk (TUG, FTSTS, 10MWT, Mini-BESTest). Participants will fill out the FES-I questionnaire together with the researcher during a telephone call (Table 1).

Clinical feasibility of the Strolll AR platform according to the participants will be assessed in terms of user experience [i.e., the User Experience Questionnaire (UEQ); (37)], technology acceptance and use [i.e., questionnaire based on the Unified Theory of Acceptance and Use of Technology model (UTAUT; (38))], top-3 barriers and facilitators of Strolll AR, and intervention-specific questions regarding Strolll AR, including cueing if used during the intervention (see Supplementary material S3). Participants will also report their falls history during the intervention period. The questionnaires of the final assessment are completed through a telephone call with the participant to ensure comprehensibility, which was first assessed in think-aloud sessions with a number of participants (39). In light of the potential future implementation in the clinical pathway, therapists will also be asked about their experience with Strolll AR through a purpose-made questionnaire (see Supplementary material S4), including the technology acceptance and use questionnaire, the top-3 barriers and facilitators (assessed before training their first participants and after training their last participant), and the UEQ (assessed after their last participant completed the study). Furthermore, a focus group with the therapist will be organized after the study for an in-depth evaluation of the top-3 barriers and facilitators.

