#### Baseline assessment (T0): characterization and effectiveness

2.2.2

The baseline assessment serves to characterize the study sample and to provide baseline values for evaluating the effectiveness of Strolll AR (see also Table 1). Study parameters used to characterize the participants are demographics (i.e., age, gender, disease duration) and current medication use [i.e., the Levodopa Equivalent Daily Dose (LEDD)]. Questionnaires to describe the participant population are the Montreal Cognitive Assessment [MoCA; (27), lower scores reflect cognitive decline], Movement Disorders Society Unified Parkinson Disease Rating Scale [MDS-UPDRS; (28), higher scores reflect more severe impairment], New Freezing of Gait Questionnaire [NFOGQ; (29), non-zero scores define freezers], Physical Activity Scale for the Elderly [PASE; (30), higher scores reflect greater self-reported physical activity], and 12-month falls history. All these outcomes will be collected using online questionnaires, except for the MoCA and MDS-UPDRS part Ia, III, and IV, which will be administered in the clinic by the therapist. To be able to evaluate the potential effects of Strolll AR for improving indicators of gait, balance, and falls risk, the following standard clinical tests will be administered by the therapists: Timed Up-and-Go test [TUG; (31), in seconds; a faster completion time reflects better performance], Five Times Sit-to-Stand test [FTSTS; (32), in seconds; a faster completion time reflects better performance], 10-meter walk test [10MWT; (33), in seconds; a faster completion time reflects better performance] and Mini Balance Evaluation Scale Test [(Mini-BESTest; (34), higher scores reflect better performance]. In addition, participants will fill out the Falls Efficacy Scale International [FES-I; (35), higher scores reflect higher concern of falling].

**Table 1 tab1:** Overview of T0, T1, and T2 tests and questionnaires to characterize the study sample and to evaluate the effectiveness and clinical feasibility of the Strolll AR intervention.

	T0	T1	T2
Study sample characterization			
Demographics (age, gender, disease duration)	X		
LEDD	X		
MoCA	X		
MDS-UPDRS	X		
NFOGQ	X		
PASE	X		
12-month falls history	X		
Effectiveness			
TUG*	X	X	X
FTSTS	X	X	X
10MWT	X	X	X
Mini-BESTest	X	X	X
FES-I	X	X	X
Clinical feasibility			
Falls history during usual-care and intervention periods		X	X
Strolll AR evaluation questionnaire			X
UEQ			X
Technology acceptance and use questionnaire			X

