#### Midterm assessment (T1): effectiveness

2.2.4

For the midterm assessment, the standard clinical tests of gait, balance, and falls-risk indicators (TUG, FTSTS, 10MWT, Mini-BESTest) (Table 1) will again be administered by the therapist. In addition, the participants are asked to fill out the FES-I and 6-week falls history (to assess falls during the usual-care period) questionnaires at home (Table 1).

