**Figure 4 fig4:**
[figure not shown]
Strolll AR gait-and-balance exercises: Smash! [without **(A)** and with **(B)** assistive AR cues], Mole Patrolll **(C)**, Hot Buttons **(D)**, Basketballl **(E)**, Puzzle Walk **(F)**, Wobbly Waiter **(G)**, and Cue Challenge **(H)**.

Participants will be invited by their therapist to use Strolll AR minimally 5 times a week for 30 active minutes per day, resulting in the recommended 150 minutes per week (1, 7, 8). They can perform the exercises anytime during the day, in one bout or in multiple chunks during the day, with complementary AR cueing when deemed beneficial. The precise exercises, exercise duration, difficulty level, and order will be prescribed by the therapist via the Strolll web portal (Figure 5). Therapists were by default recommended to prescribe all AR exercises, as each AR exercise targets different aspects (see Supplementary material S2). However, they were allowed to make adjustments, if necessary, to align with the participant’s abilities and needs, as well as for practical considerations. The prescribed exercises will be evaluated and adjusted on a weekly basis in telephone calls, e-consults or during an onsite therapy session using information of the participant in combination with the feedback from exercises that are reported in the Strolll web portal, such as adherence and game-play and functional performance metrics (cf. Supplementary material S2). Adherence will be defined as the percentage of performed over prescribed gait-and-balance exercises [i.e., both frequency and session-duration adherence; (15)]. The data on game-play level and performance will be used to evaluate whether the exercise program was both progressive (increase in level) and achievable (consistently high game-play performance scores) as intended. The weekly contact moments with the therapist will also be used to ask if participants experienced any adverse events (safety flags). Specifically, safety will be evaluated as the number of adverse events due to the Strolll AR intervention, such as falls, dizziness, eye strain, and headache. Potential technical issues will be documented by the researcher, who will be available to provide technical support during the study based on email or telephone contact with the participants.

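### FES-I is filled out at home at T1 but with the researcher by telephone at T2, so any shift due to mode of collection cannot be separated from the Strolll AR effect

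*Protocol article*

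**What the plan says.** Section 2.2.4 (T1): "the participants are asked to fill out the FES-I and 6-week falls history (to assess falls during the usual-care period) questionnaires at home".

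Section 2.2.7 (T2), on the FES-I: "Participants will fill out the FES-I questionnaire together with the researcher during a telephone call". On the final questionnaires in general: "The questionnaires of the final assessment are completed through a telephone call with the participant to ensure comprehensibility". Falls history is one of the T2 reports: "Participants will also report their falls history during the intervention period".

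Section 2.2.2 (T0) says only: "In addition, participants will fill out the Falls Efficacy Scale International". It mentions no researcher and no telephone call for this instrument, but it does not name the mode either.

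Section 2.7.3 lists FES-I among five effectiveness outcomes. The control group contributes its T0-T1 change and the intervention group its T1-T2 change, compared by independent-samples t-tests over 20 concealed randomizations. A secondary repeated-measures ANOVA uses the second reverse Helmert contrast as the intervention effect. Section 2.7.2 compares average weekly falls between the usual-care and intervention periods by a paired t-test. Under section 2.1 all participants go through the same sequence. The article describes no common mode and no adjustment or sensitivity analysis for the difference.

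**The concern.** In a parallel-group trial, a switch of mode at the last visit would affect both arms and largely cancel. Here it cannot cancel, because the comparator is an earlier period in the same people and the switch occurs only at the end of the later period. FES-I is self-reported concern about falling, and at T2 it is collected by a member of the trial team who, like the participant, knows that the intervention has just ended. The blinding in section 2.1 covers the analysis labels, not this knowledge.

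At stake is one of the five effectiveness outcomes. A difference between periods could appear, or a real one be hidden, through the way the answers were obtained. Section 2.1 discusses time-dependent confounding only as disease progression, which it regards as conservative. A mode shift has no such guaranteed direction.

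As a secondary point, the paired falls comparison sets a questionnaire completed at home against one completed by telephone.

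**Working it through.** **Inputs.** Visit order, change scores and tests are from sections 2.1 and 2.7.3. Section 2.4 gives 100 recruited and three losses of about 10 each: 100 − 30 = 70 completers, or 35 per group at 1:1. Alpha is 5%, two-sided. The article gives no FES-I standard deviation and no size for a mode shift, so the shift below is an assumption.

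**The plan's own figure.** The only stated sample size is for TUG. With d = 2.57/3.4 = 0.756 (stated as 0.755), 80% power and two-sided 5%, the two-sample t-test needs 28.53, so 29 per group and 58 in total. This reproduces the plan. It does not bear on FES-I.

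**Where the shift goes.** Let m be the mean shift from telephone completion with the researcher relative to completion at home, and suppose no true effect. If T0 has the same mode as T1:

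- control change (T0 to T1): 0
- intervention change (T1 to T2): m
- between-group difference: m − 0 = m
- second reverse Helmert contrast, T2 − (T0 + T1)/2: m − 0 = m

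Relabelling who contributes which period leaves these expectations the same, so averaging over 20 randomizations leaves m in place.

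**If T0 was collected differently.** Let a be the T0 offset relative to completion at home. The control change is then −a, the between-group difference m + a, and the Helmert contrast m − a/2. The T1-T2 change still contains m.

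**Illustration, two-sample test.** Express m as δ, in SDs of the change score. The noncentrality is δ × √(35/2) = 4.183δ on 68 degrees of freedom.

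| δ (assumed) | Noncentrality | Rejection rate with no true effect |
|---|---|---|
| 0 | 0 | 5% |
| 0.2 | 0.837 | 13.1% |
| 0.3 | 1.255 | 23.6% |
| 0.5 | 2.092 | 54.1% |

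**Illustration, second Helmert contrast.** Assume compound symmetry with correlation ρ and score SD σ. The change SD is σ√(2(1−ρ)) and the contrast SD is σ√(1.5(1−ρ)). Their ratio is √0.75 = 0.866 whatever ρ is. The noncentrality is (δ/0.866) × √70 on 69 degrees of freedom, ignoring the condition that the main effect of Time be significant first.

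| δ (assumed) | Noncentrality | Rejection rate with no true effect |
|---|---|---|
| 0.2 | 1.932 | 48% |
| 0.3 | 2.898 | 82% |
| 0.5 | 4.830 | 99.7% |

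The within-subjects analysis is the more exposed of the two, because its precision sharpens the test against a constant bias as well as against a true effect.

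**With one mode at all visits,** m and a are both zero and the two-sample rate returns to 5%.

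**The case against.** **T0 mode.** The article does not state it, so the claim that the shift lies wholly in the intervention period rests on inference. This stands as a qualification. It does not affect the T1/T2 difference, which is explicit.

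**Direction and mechanism.** A reader might infer that the telephone call inflates the benefit through social desirability. The documents do not support that. They give neither sign nor size, and completion together with the researcher need not mean that answers are spoken aloud. A shift could equally mask a benefit.

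**Falls.** A reader might infer that usual-care falls rest on unprompted recall while intervention-period falls are captured by weekly questioning. The T1 instrument is a dedicated 6-week falls questionnaire. Section 2.2.6 does say: "The weekly contact moments with the therapist will also be used to ask if participants experienced any adverse events". Those contacts serve the count of adverse events due to the intervention, and nothing says that their answers enter the paired comparison. That comparison belongs to safety reporting, where fuller capture during the intervention would count against Strolll AR. Only the T1/T2 mode difference stands.

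**Reason for the call.** Comprehensibility is a legitimate reason to use the telephone. It argues for the same help at every visit, not only the last.

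**Scope.** TUG is primary, and it, FTSTS, 10MWT and Mini-BESTest are administered by the therapist at all three visits. This stands and limits the point to FES-I and reported falls.

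**Conclusion.** The point holds for FES-I and, secondarily, for the falls comparison. The T1-T2 change combines the intervention with a change in how the answers are collected, and neither planned analysis can separate them. If T0 was self-completed like T1, the bias equals the full mode shift in both analyses. The rejection rates above show sensitivity to assumed shifts of 0.2 to 0.5 SD of the change score. They do not estimate what will happen in this trial.

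A reader might go further and call FES-I uninterpretable against usual care. With the size of the shift unknown, that is too strong. The supportable statement is that a difference between periods is confounded with mode of collection. The primary conclusion on TUG is not affected.

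**What to change.** Collect FES-I and falls history by the same mode at T0, T1 and T2, and state that mode for each visit. The simplest form is to have participants complete the same questionnaires themselves at T2, before the telephone call, and to keep the call for the user-experience, acceptance and Strolll-specific items. No new instrument is needed. The cost is slightly less help with comprehension at T2.

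The last T2 assessment was expected in February 2025 (section 2.3), so some or all data may already exist. Switching partway would leave mixed modes at T2. For data already collected, record and report the mode for each visit, and state beside the FES-I and falls results that differences between periods are confounded with mode of collection. This costs a variable and a sentence.

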### Participants

2.3

We aim to include 100 people with Parkinson’s disease in this pragmatic RCT. To be eligible to participate, a person must meet the following criteria:21 years or olderhave command of the Dutch languagediagnosed with Parkinson’s disease according to the UK Parkinson’s Disease Brain Bank criteria (stages 1–3 on the Hoehn and Yahr scale)bothersome gait or balance impairments (i.e., negatively affecting their ability to perform their usual daily activities as indicated by the person with Parkinson’s disease and/or their therapist).

A potential participant who meets any of the following criteria will be excluded from participation:inability to comply with the protocol, i.e., additional neurological diseases and/or orthopedic problems seriously interfering with gait functioninsufficient physical capacity to safely perform the intervention (e.g., frequent faller) or severe cognitive impairments (as observed by the therapist)visual or hearing impairments (after corrective aids)inability to walk independently for 30 min (in bouts of 5–10 min)severe visual hallucinations or illusionsno stable dosage of medication.

Finally, in case potential participants are susceptible to hallucinations, have a history of seizures, have deep brain stimulation, or a pacemaker, it should be discussed with their therapist if they can participate, as per Strolll’s Instructions For Use (DOC-IFU-00021 (NL), Revision 01, Date of Issue 062024). Participants are not allowed to participate in other intervention studies during the study.

Participants will be recruited by their own therapist (see the flowchart in Figure 3 for the procedure). Approximately 10 physical or exercise therapy clinics will participate, recruited via regional ParkinsonNet meetings and using a recruitment text. Clinics will be primary care practices that have therapists affiliated with ParkinsonNet [Dutch society for Parkinson’s therapists (36)]. Only clinics that indicate that they have the capacity to include minimally 5–10 participants within 6–9 months will be included. Therapists will be trained on how to administer the clinical tests (they are already familiar with most if not all tests as these are typically used tests in clinical practice) to ensure a high interrater reliability, and in applying the in- and exclusion criteria for the selection of eligible participants. In addition, therapists will be trained by the researchers on how to use the AR glasses, the Strolll AR application, and the Strolll web portal for remote prescription of and feedback about the Strolll AR intervention. After this initial training, therapists will take the AR glasses home to practice and become familiar with both the Strolll AR application and the Strolll web portal themselves. After practicing for 1–2 weeks, the researchers will contact the therapist again to discuss the use of the Strolll AR platform and to offer support during the first in-clinic session with Strolll AR with a participant to ensure therapists are well-versed with the study protocol and the Strolll AR platform. Recruitment started in May 2024 and the last T2 assessment is expected in February 2025.

### Sample size calculation

2.4

A convenience sample of 100 participants will be included and measured from approximately 10 clinics in a time frame of 9 months. This sample size will give the therapists of the clinics enough experience with the Strolll AR platform and intervention to evaluate feasibility from a therapists’ perspective (e.g., usability, acceptability, safety). For our effectiveness outcomes, an a-priori required sample-size calculation in G*Power 3.1.9.7 showed that 58 participants (i.e., 29 per group) is sufficient for identifying statistically significant between-group differences (usual care vs. Strolll AR intervention). This is based on 80% power and a two-tailed alpha error of 5% and a minimal improvement of 2.57 s in TUG [i.e., the average of the smallest detectable TUG difference of Lim et al. (40) and Huang et al. (41)] and an effect size of 0.755 [Cohen’s *d* statistic; SD of 3.4 s; (41)]. Accounting for approximately 10 dropouts during the usual-care period, approximately 10 exclusions during the pre-intervention in-clinic phase (i.e., participants deemed unable to take the glasses home after one-to-three in-clinic training sessions) and approximately 10 dropouts during the intervention period at home [estimates based on Hardeman et al. (15)], recruiting a total of 100 participants should be sufficient for obtaining the minimal groups sizes required for identifying between-group differences. As dropout rates are taken into account, participants who are not completing the study will not be replaced. Plans to reduce dropouts are a voucher as a token of appreciation for their participation, updates about study progression via a newsletter send to participants and therapists every 2 months to keep them involved in the study and having weekly online or onsite check-ins with the participating therapists.

### Discontinuation or modification of allocated intervention

2.5

Participants can leave the study at any time for any reason if they wish to do so without any consequences. The researcher can decide to withdraw a participant from the study for urgent medical reasons or when medication dosage is changed during the study. Participants that are withdrawn will not be replaced, because the sample-size calculation takes such dropouts into account. Reasons for drop out or withdrawal will be collected. Dropouts during the intervention period will be asked to complete the UEQ and Strolll AR evaluation questionnaire to reduce potential bias in the study’s participant experience results which could become manifest if only data from participants completing the intervention would be taken into account. For the other clinical tests and questionnaires, dropouts will lead to missing data.

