Top-3 barriers and facilitators of Strolll AR			X

LEDD, Levodopa Equivalent Daily Dose; MoCA, Montreal Cognitive Assessment; MDS-UPDRS, Movement Disorders Society Unified Parkinson Disease Rating; NFOGQ, New Freezing of Gait Questionnaire; PASE, Physical Activity Scale for the Elderly; TUG, Timed Up-and-Go test; FTSTS, Five Times Sit-to-Stand test; 10MWT, 10-meter walk test; Mini-BESTest, Mini Balance Evaluation Scale Test; FES-I, Falls Efficacy Scale International; UEQ, User Experience Questionnaire. *Primary outcome measure.

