Third, the pre-cursor of Strolll AR, Reality DTx^®^, was found to be a progressive-but-achievable intervention in a research setting (15), where researchers balanced and tailored task demands and capacity (i.e., not too easy to prevent boredom and not too difficult to prevent demotivation) when remotely prescribing the exercises based on weekly telephone calls with the participants and their performance data from the Strolll web portal. To determine if Strolll AR, delivered in the clinical pathway, also results in a progressive-but-achievable intervention (i.e., increasing exercise levels over weeks while maintaining high-performance scores), levels and performance scores for each game were subjected to repeated-measures ANOVAs (or their non-parametric equivalent) with the factor Time (3 levels, first, middle, last part), using paired-samples *t*-tests (or their non-parametric equivalent) post-hoc analyses for significant effects of Time. We expect to find strong main effects of Time for exercise levels (with post-hoc effects showing an increase in exercise levels), but not or less so for performance scores.

Fourth, user experience will inform on acceptability among people with Parkinson’s disease and among therapists (i.e., top-3 barriers and facilitators questionnaire and an in-depth focus group) and usability (UEQ from both participants and therapists) of the Strolll AR intervention. To evaluate participant experience, all participants who started with the Strolll AR intervention in the clinic will be analyzed collectively (i.e., intention-to-treat protocol) to avoid a selection bias of the people who completed the intervention. The UEQ will not be analyzed statistically but will be reported as descriptive outcomes and interpreted against known benchmark scores (37). Also, other participants’ or therapists’ reported outcome measures from the questionnaires will be reported as descriptive outcomes. Finally, the fraction of participants deemed eligible for performing the intervention at home after having had the in-clinic Strolll AR sessions will inform about the usability of the intervention.

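### The all-starters analysis of participant experience cannot be done for the top-3 barriers, because people who stop are not asked for them

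*Protocol article*

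**What the plan says.** Table 1 has four separate participant-reported feasibility rows at T2 only: the Strolll AR evaluation questionnaire, the UEQ, the technology acceptance and use questionnaire, and "Top-3 barriers and facilitators of Strolll AR". Section 2.2.7 also names them as distinct items.

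Section 2.7.2 states that user experience informs on acceptability and usability. Usability is tied to the UEQ. Acceptability is tied to two sources: "i.e., top-3 barriers and facilitators questionnaire and an in-depth focus group". The analysis set follows: "To evaluate participant experience, all participants who started with the Strolll AR intervention in the clinic will be analyzed collectively". The stated reason is "to avoid a selection bias of the people who completed the intervention".

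Section 2.5 sets out what is collected from people who stop: "Dropouts during the intervention period will be asked to complete the UEQ and Strolll AR evaluation questionnaire". The purpose given is "to reduce potential bias in the study’s participant experience results which could become manifest if only data from participants completing the intervention" were used. It then adds: "For the other clinical tests and questionnaires, dropouts will lead to missing data". Section 2.7 excludes missing data analysis by analysis. Section 2.5 also says that reasons for dropout or withdrawal will be recorded.

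**The concern.** The analysis set and the collection rule do not match. An analysis of all in-clinic starters needs data from those who stopped. For the top-3 barriers, section 2.5 says those data will not exist, and section 2.7 provides nothing to fill the gap. The plan gives avoidance of completer selection as its reason both for the analysis set and for contacting dropouts, yet it leaves out of that contact the instrument it uses for acceptability.

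Feasibility is a primary study parameter in the abstract. The Discussion calls clinical feasibility from the participants' perspective a key focus and expects the questionnaire feedback to guide development and implementation. A barrier ranking taken only from people who finished could differ from the ranking among all who started, and a reader told that the analysis covers all starters would not know this.

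**Working it through.** **Inputs, all from section 2.4.** 100 recruited; about 10 lost during usual care; about 10 stopped in the in-clinic phase; about 10 lost during the home period.

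**The plan's own figure.** 100 − 10 − 10 − 10 = 70 finishers, above the 58 that the plan requires for the TUG comparison. That figure is not in dispute.

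**Who is in the promised set.**
- Started in the clinic: 100 − 10 = 90
- Went home with the glasses: 90 − 10 = 80
- Finished: 80 − 10 = 70

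**Coverage of the top-3 barriers and technology acceptance under section 2.5.**
- Of in-clinic starters: 70/90 = 77.8%, so 20/90 = 22.2% missing
- Of home starters: 70/80 = 87.5%, so 10/80 = 12.5% missing

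**Coverage if more people are asked** (upper limits, assuming everyone answers).
- Home dropouts added: 80/90 = 88.9%
- Those stopped in the clinic phase added as well: 90/90 = 100%

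**What the gap could do to one result.** The shares here are assumed; none is in the documents. Let 20% of the 70 finishers name a given barrier (14 people), and let a share q of the 10 home dropouts name it. Among the 80 home starters the share is (14 + 10q)/80:
- q = 20%: 16/80 = 20.0%
- q = 40%: 18/80 = 22.5%
- q = 80%: 22/80 = 27.5%

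Over the promised set of 90, with q applied to all 20 non-finishers, the share is (14 + 20q)/90. At q = 20% it is 18/90 = 20.0%; at q = 80% it is 30/90 = 33.3%. The limits with no assumption about q are 14/90 = 15.6% (q = 0) and 34/90 = 37.8% (q = 100%). The finishers' 20% could therefore be too high, too low or right.

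**An ambiguity about the clinic phase.** Section 2.2.5 says that the intervention starts with the supervised in-clinic sessions. Section 2.4 calls that phase pre-intervention. Section 2.5 asks the two questionnaires of dropouts during the intervention period. If people stopped in the clinic phase fall outside that term, even the UEQ and evaluation questionnaire would miss about 10 of the 90.

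**The case against.** **The all-starters set may be meant only for the UEQ and the evaluation questionnaire.** Section 2.5 attaches the idea of participant-experience bias to those two, and in section 2.7.2 the UEQ sentence directly follows the analysis set. For technology acceptance and use this carries weight: it comes in only through a general sentence on other reported outcomes, with no analysis set stated. For the top-3 barriers it carries less, because the same paragraph names them as the acceptability measure just before it defines the set. At the least, the text needs to say which instruments the set covers.

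**The evaluation questionnaire might already contain the barrier and acceptance items.** Its content is in Supplementary material S3, which is not shown, and the therapists' questionnaire is described as including several such components. This cannot be excluded, but Table 1 and section 2.2.7 list the participant instruments separately.

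**Other data capture why people stop.** This stands in part. Reasons for withdrawal, adverse events, technical issues, the reason when home use is judged unsuitable, and the fraction eligible for home use are all recorded. A decisive barrier need not go unseen. But none of these is the same ranking, and they cannot be pooled with the finishers' answers. The focus group does not help either: section 2.2.7 describes it as one with therapists.

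**A shorter set for people who have left is a reasonable limit on burden.** That is a fair choice, but the analysis set should then be described to match it.

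A reader might infer that barriers are under-counted and acceptance overstated. The documents do not support that. They give no responses from people who stopped, and withdrawals under section 2.5 include urgent medical reasons and medication changes, which need not reflect any barrier in the platform.

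**Conclusion.** The point holds as a mismatch between sections 2.5 and 2.7.2. It is clearest for the top-3 barriers and weaker for technology acceptance and use. On the plan's own approximate attrition, these two instruments would be available for about 70 of 90 in-clinic starters. The missing 20 divide about equally between home dropouts and people stopped in the clinic phase.

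This rests on the section 2.4 estimates being roughly met, and on the four instruments being separate, as Table 1 shows them. The direction and size of any bias are unknown.

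A reader might also infer that user experience as a whole is completer-only. It is not: home dropouts are asked for the UEQ and the evaluation questionnaire. The affected outcomes are descriptive, and the TUG sample size and the effectiveness analyses are untouched. The change is worth making because it is cheap and follows the plan's own rationale.

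**What to change.** In section 2.5, ask everyone who started in the clinic and then stopped, whether in the clinic phase or at home, for the top-3 barriers and facilitators and the technology acceptance and use items, in the same contact as the UEQ and evaluation questionnaire. State explicitly that people stopped in the clinic phase are included.

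In section 2.7.2, report both instruments with numerator and denominator for all starters, and separately for finishers and for those who stopped.

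If these data can no longer be collected, limit the all-starters statement to the UEQ and evaluation questionnaire (with the number of starters who answered) and label the barrier and acceptance results as finishers only.

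Cost: a few more minutes for about 20 people and no new instrument. Some will not respond, so full coverage is an upper limit. The alternative costs only a change of wording.
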